##### Exploratory aim 1 (dosage)

With respect to examining dosage of tai chi, we will compare the change in all outcomes between the two tai chi groups (12-week versus extended 24-week intervention) using ANCOVA and the Wilcoxon rank sum test as appropriate, similar to our primary aims. We will further assess adherence to the continued classes from 12 to 24 weeks. We will also analyze home practice hours (in both groups), and total practice hours (class plus home practice in the 24-week class group) and compare groups using the Wilcoxon rank sum test. Clinical data obtained through patient interview will be analyzed using descriptive statistics.

Particularly in the intervention groups, we will describe patient attendance at classes and compliance with home practice, and examine whether compliance or dosage is associated with clinical outcome.

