**Figure 2 Fig2:**
[figure not shown]
**The BEAM study design.** The primary aims of this randomized controlled trial are to evaluate the efficacy, safety and feasibility of a 12-week tai chi exercise program as compared to a time- and attention-matched education control. At 12 weeks, subjects in tai chi undergo a second randomization to either continue with tai chi for an additional 12 weeks (total 24 weeks), or to receive usual care. (Exploratory Aim 1: Tai Chi Dosage). To explore the impact of a simplified seated mind-body breathing intervention, a third randomly assigned group receives a 12-week mind-body breathing program (Exploratory Aim 2). After the initial 12 weeks of both education and mind-body breathing, subjects receive usual care for the following 12 weeks. All participants undergo testing at baseline, 12 weeks, and 24 weeks.

Our primary efficacy outcomes are COPD-specific quality-of-life (chronic respiratory questionnaire (CRQ)) and exercise capacity (6-minute-walk test). Secondary outcomes examining further psychosocial and physiological effects of tai chi include symptoms of dyspnea, fatigue, mood, functional status, strength and flexibility, self-efficacy, social support, and pulmonary function. Cardiopulmonary exercise testing is also done in a subset of patients (n = 50). Safety and feasibility will be assessed by successful recruitment and randomization, adherence to the protocol and attendance at classes (at least 70%), and demonstrated safety through systematic adverse events (AE) monitoring and reporting.

We hypothesize that there will be improved patient-centered outcomes (quality of life and exercise capacity) in the tai chi group as compared to education control and that the study will be feasible and safe in COPD. Those who receive continued tai chi in phase 2 will have increased 24-week adherence and improved outcomes. There may be similar benefit in the MBB group in symptoms of dyspnea and psychosocial measures, but the tai chi intervention will have trends towards more benefit on exercise capacity, cardiopulmonary function, strength, and flexibility.

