### Randomization and allocation concealment

Randomization occurs after baseline testing. Participants are randomized to one of three group classes: tai chi, MBB, or education, in a 2:1:1 ratio. Group assignments are generated by a permuted blocks method with randomly varying block size, and sealed in numbered, opaque envelopes. Intervention classes begin within 3 weeks of baseline testing. At the end of phase 1, participants in the tai chi group undergo a second randomization to either continue tai chi class once weekly, or to resume usual care. Participants are informed at baseline of the two randomization processes and that the intervention may be either 3 or 6 months long.

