### Statistical analysis

#### Sample size and power

This study is powered on our pre-specified primary outcomes of overall CRQ (chronic respiratory questionnaire) score and 6-minute walk-test distance. Our effect estimates and standard deviations are based on pilot data of 12-weeks of tai chi versus usual care in patients with COPD [52]. Enrollment of 125 participants will provide approximately 93% power to detect differences between groups of approximately 50 meters change in the 6-minute walk test and 0.9 point change in total CRQ score (mean response value). Our primary comparison will be between the tai chi and education groups, from baseline to 12 weeks in phase 1. It is widely accepted that a change in the 6-minute walk test of 54 meters is clinically significant [81, 101–104]. For the CRQ, Redelmeir *et al*. reported that a 0.5 point change is clinically meaningful [104]. Our study has over 96% power to detect a difference of 54 meters and 99% power to detect a difference of 68 meters (the difference observed in our pilot). These calculations allow for a 5% loss of statistical efficiency of the nonparametric test compared to a *t*-test (for the 6-minute walk), 10% dropout rate, and a conservative Bonferroni correction for multiple outcomes.

For our exploratory dosage aim, we expect to have about 82% power to detect differences between groups of a 50-meter change in 6-minute walk and 0.9 point change in total CRQ. This sample size of 21 per group (12 weeks versus 24 weeks of tai chi) accounts for a 5% loss of statistical efficiency. We expect to have limited power for our second exploratory aim comparing tai chi to the MBB group.

Prior to analyzing the outcomes, we will examine baseline demographic, functional, and clinical variables as well as known prognostic factors (such as baseline GOLD stage and baseline peak VO_2_) by randomized group. Our primary analyses will examine changes between baseline and 12 weeks.

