#### Primary aims

##### Efficacy

Changes in total scores on the CRQ will be analyzed using analysis of covariance (ANCOVA), comparing the change from baseline to 12 weeks among the two treatment groups tai chi versus education, adjusted for the baseline value of the outcome (and, if necessary, baseline characteristics found poorly balanced between groups). For the 6-minute walk, the change from baseline to 12 weeks is known to be skewed, so we will use a nonparametric approach and use a Wilcoxon rank sum test to compare the two treatment groups at α = 0.05 (without the Bonferroni correction, given the pilot feasibility nature of the study). As complements to these main approaches, we may use bootstrap analysis to evaluate confidence intervals and the cumulative distribution function with evaluation of the area under the curve for each study arm to show the distribution of patients who improve.

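### The dosage aim borrows the primary analysis without naming the week-12 value as reference or covariate, although its groups are randomised at week 12: a loss of precision, not a bias

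*Protocol article*

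**What the plan says.** The two tai chi durations are not formed at study entry. Under Randomization and allocation concealment, "At the end of phase 1, participants in the tai chi group undergo a second randomization to either continue tai chi class once weekly", the alternative being a return to usual care. The caption of Figure 2 states "All participants undergo testing at baseline, 12 weeks, and 24 weeks", so a week-12 value is scheduled for every participant who is re-randomised.

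For the analysis, Exploratory aim 1 (dosage) says "we will compare the change in all outcomes between the two tai chi groups", and gives the method as "using ANCOVA and the Wilcoxon rank sum test as appropriate, similar to our primary aims". The primary method is set out under Efficacy. The CRQ change is analysed by ANCOVA, "adjusted for the baseline value of the outcome". For the 6-minute walk the plan is to "use a Wilcoxon rank sum test to compare the two treatment groups at α = 0.05", with no covariate. The primary interval is baseline to week 12.

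Sample size and power promises "about 82% power to detect differences between groups of a 50-meter change in 6-minute walk" and 0.9 CRQ points, with 21 per group. It does not state the standard deviation or the interval on which this rests.

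**The concern.** The reference point for a randomised comparison is the last measurement before allocation. For the dosage groups that is week 12, after both have been assigned the same 12 weeks of tai chi. The article does not name the week-12 value as the start of the change or as a covariate for this aim. The primary interval cannot be carried over as it stands, because it ends at the second randomisation. The nearest substitute is change from week 0 to week 24, adjusted for week 0 (CRQ) or unadjusted (walk).

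On that default, differences between patients in phase 1 response, which precede the duration randomisation, stay in the comparison as noise. The article presents information on training duration as one of the trial's contributions, and this is its only randomised evidence on the question. The groups are small, so avoidable variance matters.

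**Working it through.** **1. The plan's own figure.** The SD is not stated, so it is back-solved from the primary power statement. Inputs: 63 and 31 patients, 10% dropout, 5% efficiency loss, Bonferroni taken as 0.05/2 = 0.025, two-sided, normal approximation.

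- Effective sizes: 63 × 0.90 × 0.95 = 53.9 and 31 × 0.90 × 0.95 = 26.5.
- Power = Φ(Δ / (SD·√(1/n1 + 1/n2)) − z). Setting this to 93% at 50 m gives SD ≈ 56.7 m. The same SD gives 96.2% at 54 m and 99.8% at 68 m, against the stated over 96% and 99%.
- Dosage aim, 21 per group taken as already net of the efficiency loss, α = 0.05: 50 / (56.7 × √(2/21)) = 50 / 17.5 = 2.86; 2.86 − 1.96 = 0.90; Φ = 81.5%. The CRQ (SD ≈ 1.02 points) also gives 81.5%.

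So the 82% reproduces with the SD implied for the 0-to-12-week change. Some other combinations of α and attrition also land near 82%, so this is a consistent reading, not proof of how it was derived.

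**2. Residual variances.** Assume equal variances (set to 1) and the same correlation ρ between any two of weeks 0, 12 and 24. The article gives no correlations.

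- Raw change: 2(1 − ρ)
- ANCOVA on week 0: 1 − ρ²
- ANCOVA on weeks 0 and 12: 1 − 2ρ²/(1 + ρ)

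| ρ | raw change | week 0 | weeks 0 and 12 | cut vs week 0 | cut vs raw change |
|---|---|---|---|---|---|
| 0.5 | 1.00 | 0.75 | 0.667 | 11% | 33% |
| 0.7 | 0.60 | 0.51 | 0.424 | 17% | 29% |
| 0.9 | 0.20 | 0.19 | 0.147 | 22% | 26% |

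The price is about one degree of freedom out of roughly 40. These are normal-theory variances, so they are only a guide for the rank analysis of the walk.

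**3. Swapping versus adding.** With equal correlations, either visit alone leaves 1 − ρ², so replacing week 0 by week 12 gains nothing. At ρ = 0.7, power for 50 m is 87% with either covariate and 92.5% with both. A swap helps only if r(12,24) exceeds r(0,24). The next table holds the SD of the 0-to-12-week change at 56.7 m (visit SD = 56.7/√(2 − 2r(0,12))), with 21 per group and α = 0.05.

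| r(0,12) / r(12,24) / r(0,24), assumed | ANCOVA: week 0 → week 12 | unadjusted change: 0–24 → 12–24 |
|---|---|---|
| 0.6 / 0.7 / 0.5 | 84% → 95% | 72% → 91% |
| 0.7 / 0.8 / 0.6 | 79% → 96% | 70% → 94% |
| 0.7 / 0.7 / 0.49 | 72% → 87% | 59% → 82% |
| 0.8 / 0.8 / 0.64 | 65% → 85% | 57% → 82% |

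**4. Chance imbalance at week 12.** The standard error of the difference between two groups of 21 is √(2/21) = 0.31 SD. For the phase 1 change in walk distance it is 56.7 × 0.309 = 17.5 m, about a third of the 50 m target.

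**The case against.** The strongest reply is that the article does not commit to the study baseline. The dosage section gives no start, no end and no covariate, and the primary interval cannot transfer. The reference to the primary aims may therefore mean only the type of method, with the week-12 value as the natural baseline. Such details of an exploratory aim are commonly settled in the full protocol or SAP, neither of which is shown. This stands to the extent that a reader might infer a fixed decision to adjust for week 0, and the text does not support that. Week 0 is the default that the cross-reference points to, no more.

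A reader might also infer that a chance difference at week 12 would bias the result towards or against longer training. It would not. Both the week-0 and week-12 values precede the second randomisation, so change from either is unbiased for the randomised contrast, and the chance difference is already reflected in the standard error. Total change from study entry is a legitimate question too.

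Nor do the 11 to 22% measure the cost of a wrong baseline: under equal correlations they come wholly from adding a second covariate. The 26 to 33% also include the move from raw change to ANCOVA.

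What the reply does not remove is that the section states a method by cross-reference. On either reading that method uses at most one pre-randomisation value as covariate for the CRQ and none for the walk, although two are collected.

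**Conclusion.** The point holds as a minor one. The dosage groups are randomised at week 12, and the analysis is carried over from the primary aims without naming the interval or the covariate. By default it leaves out the last value before allocation. The consequence is lost precision and exposure to chance imbalance, not bias.

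Under equal between-visit correlations of 0.5 to 0.9, the avoidable residual variance is 11 to 22% against a week-0 ANCOVA and 26 to 33% against raw change. If adjacent visits correlate more strongly than weeks 0 and 24, the loss from relying on week 0 is larger, as the scenarios show. All of these correlations are assumptions.

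The 82% power is not shown to be wrong. It matches the SD implied for a 12-week change and may not describe a 0-to-24-week comparison. The severity is limited because the aim is exploratory in a pilot trial, and because the same section also relates practice and compliance to outcome, though not by randomisation.

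**What to change.** State for Exploratory aim 1:

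- The outcome is the week-24 value, analysed in all re-randomised tai chi participants.
- The CRQ is analysed by ANCOVA with the week-12 value as covariate and the week-0 value as a second covariate.
- The 6-minute walk is analysed by rank ANCOVA on the same covariates or, at the least, by the Wilcoxon test on the change from week 12 to week 24.
- The 82% power refers to the SD for that interval and analysis, and is recomputed if it was taken from the 0-to-12-week change.

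The cost is a sentence or two and about one degree of freedom. All the measurements are already scheduled.

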##### Exploratory aim 2 (MBB)

We will obtain the point estimates for the change in outcomes, that is, mean change in CRQ and median change in the 6-minute walk between baseline and 12 weeks in the MBB group. We expect these means/medians to be intermediate between changes in the tai chi group and changes in the education group. Even though we are not powered to detect differences between groups, we will conduct exploratory analyses to gather preliminary estimates of effect. We will use ANCOVA and Wilcoxon rank sum tests, similar to the first aim, to compare change in the CRQ and the 6-minute walk, between the MBB group and education, and between the MBB group and tai chi. We will establish overall feasibility and adherence of the MBB group by assessing willingness to participate and attendance at classes.

## Summary/Discussion

Results of this innovative study will establish feasibility and provide preliminary evidence on the efficacy of tai chi exercise to improve quality of life and exercise capacity in patients with COPD. In addition, we will capture information on potential physiological and psychosocial mechanistic pathways. The development and exploration of a seated intervention that emphasizes meditative breathing provides further insight into mechanisms of tai chi by isolating relevant elements of the larger, multicomponent intervention. Finally, the extension of intervention duration from 12 to 24 weeks will help to inform issues of optimal dosage for this population.

## Trial status

This study is currently ongoing with active recruitment.

## Abbreviations

AE: adverse event
ANCOVA: analysis of covariance
BEAM: breathing: education: awareness: movement
BIDMC: Beth Israel Deaconess Medical Center
BODE: body mass: airflow obstruction: dyspnea: exercise capacity
CES-D: Center of Epidemiology Studies-depression scale
CHAMPS: Community Health Activities Model Program for Seniors physical activity questionnaire for older adults
COPD: chronic obstructive pulmonary disease
CRQ: chronic respiratory disease questionnaire
CSES: chronic obstructive pulmonary disease self-efficacy scale
DSMB: Data Safety and Monitoring Board
ER: emergency room
FEV1/FVC: forced expiratory volume in one second/forced vital capacity
GOLD: global Obstructive Lung Disease
HIPAA: Health Information Privacy and Accountability Act
HRQL: health-related quality-of-life
IC/TLC: inspiratory-to-total lung capacity ratio
IRB: Institutional Review Board
MBB: mind-body breathing
MET: metabolic equivalent
MMRC: Modified Medical Research Council
PROMIS®: Patient-Reported Outcome Measurement Information System
TLC: total lung capacity
VO2: peak oxygen uptake.
